### Trial interventions

#### Narrative exposure therapy

NET is an evidence-based treatment for PTSD for multiple or prolonged traumatic events.^16^ Through detailed narration, traumatic memories are processed and contextualised, helping the person to develop a coherent autobiographical narrative. At the start of therapy, there is a co-construction of the person’s lifeline using physical materials, including traumatic events (represented by stones) and positive events (represented by flowers). Events are narrated in subsequent sessions in chronological order to ‘process’ the trauma memory and make meaning. We plan to offer 15 weekly individual sessions lasting 90 min. At the end of therapy, the person receives the written narrative as a documented testimony. The trial intervention will be provided as an addition to routine mental healthcare.

Face-to-face and online delivery will be offered. When online delivery is offered, e-NET guidance will be followed.^51^ Face-to-face therapy will be delivered at locations convenient for the participant resources permitting (eg, EIP team base, other NHS premises or residential locations) in line with the EIP assertive outreach model.^52^

The intervention will be delivered by a range of EIP professionals, including psychologists, CBT therapists, mental health nurses and occupational therapists (or professionals with equivalent experience, including those in the final year of training) within EIP. The manual for this feasibility trial will follow the standard NET manualised intervention,^16^ but it will also include specific guidance for addressing psychosis co-morbidity and delivery within an EIP service, in line with learning from pilot work and PPI consultation.^28 29^

NET clinicians will record information on session content, length, frequency, dates, number of sessions attended, number of sessions offered but not attended, mode (face to face/online) on a pre-defined database. All therapy sessions will be audio recorded if the participant gives written consent.

#### Treatment fidelity

NET training will take place over 2 days and will be provided by [name], UK NET trainer, in collaboration with the NET Institute and [name], one of the original developers of NET (https://www.net-institute.org). NET therapy fidelity will be monitored as follows: Treatment adherence will be monitored by asking therapists to complete a standardised session form to monitor session content after each therapy session that will be reviewed fortnightly during supervision sessions throughout the trial. Treatment competence will be assessed by a mixture of rating a random selection of therapy recordings (two sessions per therapist) using a NET fidelity scale developed by the NET Institute ([name], UK NET trainer and project collaborator, personal communication, 2023).

#### Treatment as usual

This will be the routine care that participants receive including the EIP multi-disciplinary care from mental health nurses, psychiatrists, occupational therapists and psychologists in a community setting, with associated crisis and inpatient settings if required. EIP services offer up to 3 years of multidisciplinary support, including an allocated care coordinator and offer of antipsychotic medication and psychological interventions, such as CBTp and Family Intervention for psychosis.

### Adverse events

The occurrence of adverse events (AEs) will be monitored actively and systematically, following guidance from the CONSORT^53^ with the extension for social and psychological interventions^54^ and the extension for reporting of harms.^55^ AEs are defined as any untoward medical occurrence in a patient or trial participant, which does not necessarily have a causal relationship with the intervention involved. Each AE will be assessed for severity, seriousness, causality and expectedness as described below. Severity will reflect the impact of the events on the person at the time and have three levels (mild, moderate, severe). Seriousness relates to the outcome of the event, a serious adverse event (SAE) is defined as any AE that results in death, is life-threatening, requires hospitalisation or prolongation of existing hospitalisation, results in persistent or significant disability or incapacity or consists of a congenital anomaly or birth defect. No AEs or SAEs are expected as a result of the intervention. Temporary mild distress is expected to occur at the start of treatment and as part of exposure (eg, relieving the event) during trauma focus therapies. This is not predictive of poor treatment response in trauma-focussed therapies in people with psychosis.^56^

All AEs will be recorded in the Case Report Form (CRF) and sponsor’s AE log. SAEs will be reported to the sponsor within 24 hours of becoming aware. The CI (or a clinically qualified delegate) will review all SAE reports received. We will review the notes of all participants at the end of the trial to ensure thorough reporting.

We will report the number of AEs by trial arm and also give separate numbers of events by severity of the event and causality (related to the intervention, not related, not assessable).

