#### Experience sampling methodology (ESM)

m-Path is a mobile online platform designed to collect real-time data collection on experiences, emotions and behaviours. Participants allocated to the NET arm who consent to take part in this sub-study, will be prompted by a notification from the m-path app (https://m-path.io/landing/)^47^ once daily. Participants will receive an induction on the use of m-Path at baseline. This will involve personalisation (choosing a greeting/ending message), the time of the day they’d like to complete ESM data entry (a time between 08:00 and 22:00), and they will also be able to complete a practice questionnaire. Data completion is estimated to last approximately 2 min. Daily entering of data on a mobile app (https://m-path.io/landing/) will take place from 1-week pre-NET therapy (post randomisation) to 1 week post NET therapy completion. Areas covered include PTSD and cPTSD symptoms, unusual distressing experiences of psychosis, paranoia, mood, social connection, hope and context. m-Path procedures and items were co-produced. Participants will be made aware that their individual responses will be reviewed weekly by the clinician at the start of each of the 15 NET sessions, and by an unblinded researcher on the week after therapy ends.

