#### Session-by-session monitoring

Participants allocated to NET will complete a weekly monitoring measure with the NET therapist. This will cover the same areas as in the ESM daily monitoring (that some participants will opt in to complete) in addition to three items enquiring about risk to self, cultural humility and therapeutic bond.

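### Adverse event counts by arm risk unequal detection of non-serious events, because the scheduled weekly monitoring exists only in the NET arm

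*Protocol article*

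**What the plan says.** All references are to the protocol article.

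- **Output.** Adverse events: "We will report the number of AEs by trial arm and also give separate numbers of events by severity of the event and causality". The unit is the event. No between-arm test or effect estimate is stated.
- **Definition and logging.** The same section defines an adverse event broadly, with no causal link required. It grades severity from mild upwards and sends every event to the case report form and the sponsor's log.
- **Ascertainment in both arms.** "The occurrence of adverse events (AEs) will be monitored actively and systematically", and "We will review the notes of all participants at the end of the trial to ensure thorough reporting". Table 2 schedules research assessments at 4 and 8 months in both arms.
- **Ascertainment in NET only.** Session-by-session monitoring: "Participants allocated to NET will complete a weekly monitoring measure with the NET therapist", including "three items enquiring about risk to self, cultural humility and therapeutic bond". Experience sampling methodology (ESM): for those who opt in, "their individual responses will be reviewed weekly by the clinician at the start of each of the 15 NET sessions". Treatment fidelity: therapists complete a form after each session, and it is reviewed fortnightly in supervision.
- **Expectedness.** Adverse events: "No AEs or SAEs are expected as a result of the intervention". The next sentence reads: "Temporary mild distress is expected to occur at the start of treatment and as part of exposure".

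**The concern.** A count by arm can be read as a contrast in harm only if an event has a similar chance of being recorded in each arm. Here one arm meets a trial therapist about weekly and is asked about risk to self. The other arm has no matching trial contact between assessments. Because mild events count and all must be logged, a non-serious event disclosed in a NET session belongs in the log. The same event under TAU may never come to the trial's attention.

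An event total adds a second weakness. It cannot distinguish one participant with many events from many participants with one each, and with about 25 per arm that matters.

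The expectedness sentences raise a separate question of classification. If temporary mild distress from exposure is an adverse event under the article's own definition, the statement that none are expected does not fit the sentence after it. If it is not an adverse event, the text does not say so.

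The Background states that no study has yet evaluated the safety of NET in early intervention services. These counts will therefore be carried forward as safety evidence for a main trial.

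**Working it through.** The article gives no adverse event rate, detection rate or harm threshold, so there is no stated figure to reproduce. Two simple checks follow.

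**1. Scheduled trial contacts after randomisation**

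- NET: 15 weekly sessions (Narrative exposure therapy) + 2 assessments (Table 2) = 17.
- TAU: 2 assessments.
- Ratio: 17/2 = 8.5.

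Routine early intervention care is left out because both arms receive it. ESM is also left out because it is opt-in and its listed areas do not include risk. For those who join, it adds up to 7 × (15 + 2) = 119 daily prompts, assuming 15 consecutive weeks plus one week on each side. The contact ratio shows that opportunity is unequal. It does not measure how many more events are detected.

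**2. Recorded event ratio when the true rates are equal**

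Let *b* be the share of events captured by sources common to both arms (the two assessments and the notes review). Let *e* be the share of the remaining events that only NET contact brings to light. Both are assumptions. Then

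recorded NET/TAU ratio = [*b* + (1 − *b*)*e*] / *b*

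| *b* | *e* = 0.3 | *e* = 0.6 | *e* = 0.9 |
|---|---|---|---|
| 0.3 | 1.70 | 2.40 | 3.10 |
| 0.5 | 1.30 | 1.60 | 1.90 |
| 0.7 | 1.13 | 1.26 | 1.39 |
| 0.9 | 1.03 | 1.07 | 1.10 |
| 1.0 | 1.00 | 1.00 | 1.00 |

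Worked row, *b* = 0.5: (0.5 + 0.5 × 0.3)/0.5 = 0.65/0.5 = 1.30, and (0.5 + 0.5 × 0.9)/0.5 = 0.95/0.5 = 1.90.

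In events, take 25 per arm (25 are offered NET, out of 50) and assume one true event per participant. TAU would record 25 × 0.5 = 12.5. NET would record between 25 × 0.65 = 16.25 and 25 × 0.95 = 23.75, with no true difference.

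High *b* is plausible for admissions and deaths, which a notes review should find, so the distortion there is small or nil. Low *b* is plausible for mild events that rarely reach the notes. If the count by arm uses common sources only (*e* = 0), the expected ratio is 1.00 for every *b*.

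**3. Expectedness sentences side by side**

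Each event is to be assessed for expectedness. The first sentence leaves the set of expected events empty. The second names an expected effect of the therapy that is mild, which is also the lowest severity grade. Nothing says whether that effect falls inside the definition. It arises from exposure and so occurs in NET, which means the choice moves the NET count and the category of events related to the intervention.

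**The case against.** The strongest reply is that the link from NET monitoring to the adverse event log is not written down. Neither the weekly measure nor ESM is described as a source of adverse events, and the session form exists to check adherence. The article condenses a fuller protocol that may set out how events are elicited, so silence on that procedure is not a fault. This stands in part: it rules out any claim about how much extra detection will occur. It does not remove the risk, because the article requires all events to be logged and has no rule keeping those learned in sessions out of the count by arm.

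The reply also notes that TAU participants are not unobserved. They have a care coordinator, routine multidisciplinary care and the same notes review. This stands, and it is why the concern is confined mainly to non-serious events. Nor does any section say that NET session findings reach the clinical notes, so the notes review cannot be dismissed on that ground.

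A reader might infer that the harm comparison is shown to be biased. The documents do not support that: the size depends entirely on assumed detection shares, and the table includes 1.00. A reader might also infer that the progression decision would be misled. Table 1 sets numerical criteria for recruitment, retention and therapy engagement only. It has no adverse event criterion, and the by-arm report is descriptive.

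Finally, the two expectedness sentences can be read as a carve-out that separates ordinary therapy distress from adverse events. That reading is possible, but the text does not state it.

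**Conclusion.** The concern holds as a risk of differential detection, mainly of mild and moderate events, in a descriptive count by arm. Serious events are largely protected, provided that the notes review captures them. The magnitude is unknown. With equal true rates, the recorded ratio runs from 1.00 if common sources capture everything, through 1.03 to 1.10 if they capture 90%, to about 1.3 to 1.9 if they capture half. These figures rest on assumed values of *b* and *e*, and on events learned in NET sessions being logged as the article's definition implies.

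The expectedness wording is a secondary point about classification. It needs reconciling, but it does not by itself show a bias between arms. The change is worth making because it is cheap and these counts may inform the safety case for a main trial.

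**What to change.** 1. Add a source field to the adverse event form: 4- or 8-month assessment, notes review, NET session or weekly measure, ESM, other.
2. Present the table by arm from sources applied alike in both arms (the two assessments and the notes review), beside the all-source count. List separately the events found only through NET sessions or ESM. No safety information is lost.
3. Report the number of participants with at least one event as well as the number of events, by arm.
4. Reconcile the two sentences on expectedness in the Adverse events section, and state whether temporary distress during exposure is recorded as an adverse event, so that it is classified the same way throughout. Which classification to adopt is for the investigators.

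The cost is one extra field, one extra table and a wording change. Recruitment was due to start in August 2025, so source may need to be filled in for events already logged. If the wording change counts as a protocol amendment, it goes to the same ethics committee, as the article provides.

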### Data handling

The study will be compliant with the requirements of the General Data Protection Regulation (GDPR) (2016/679) and the UK Data Protection Act (2018). All investigators and study site staff will comply with the requirements of the GDPR (2016/679) with regard to the collection, storage, processing and disclosure of personal information and will uphold the Act’s core principles. University College London (UCL) is the data controller.

The CI will be the custodian for the trial data. The CRFs, paper questionnaires and online questionnaires will not bear the participant’s name or other personally identifiable data. All paper data will be anonymised and stored in a locked filing cabinet in the CI’s office at UCL (Research Department of Clinical, Health and Educational Psychology where the main Principal Investigator (PI) [name] is based) or in the local NHS site in a location agreed by the local PI and local NHS Research and Development (R&D) team. The participant’s trial identification number will be used for identification. Anonymised data will be entered by RAs in the Research Electronic Data Capture system (REDcap) at University College London. Linked data (anonymised via participant ID) will be stored on a secure university electronic database for up to 10 years. Fully anonymised data will be kept indefinitely. Please see the study Data Management and Access Plan. Data will be deposited into the (Dataset) UCL Data Repository.

During the study, it is possible that a participant may disclose a serious risk of harm to themselves or to others. In these instances, participants’ confidentiality would be breached to share the necessary information with the relevant clinical team. The participant would be made aware of the limits of confidentiality in such instances in the Participant Information Sheet.

### Analysis

#### Quantitative analysis

Analyses will be carried out when the database has been cleaned and locked and after the statistical analysis plan has been finalised. We will use a CONSORT diagram to indicate the flow of participants through the study. We will report the numbers eligible, consenting and available for follow-up. We will document the recruitment pace and rate of consent to the study. We will report the number of participants meeting inclusion criteria via PTSD only, psychosis only and via both PTSD and psychosis routes. We will report the distribution of the number of NET sessions attended by each participant in the intervention arm, the proportion of participants who attend at least 8 out of the 15 NET sessions and therapy drop-out rates. The retention rate of participants as the proportion in each arm that provide responses at the 4-month and at the 8-month research assessment follow-ups will be reported alongside rates of item missingness (separately for each outcome measure). Furthermore, we will describe the distribution of responses on the FaM and conduct a qualitative thematic analysis to explore the responses to open-ended items. Treatment fidelity will be assessed by rating a random selection of therapy recordings (two sessions per therapist) using a NET fidelity scale developed by the NET Institute, with the distribution of the ratings described.

This study is a feasibility re and is not powered to evaluate evidence for the efficacy of NET vs TAU. Instead, we will report preliminary estimates that can inform sample size calculations for a future trial. All primary and secondary outcome measures are numeric variables and will be assessed at three time points. The 4-month follow-up will be the primary endpoint. Estimates of the treatment effect, NET versus TAU, at both follow-up points will be obtained from a multilevel model. Participants will be included in the outcome analysis if, for a given outcome, they have provided data at either the 4-month follow-up, the 8-month follow-up or both. The model can accommodate missing outcome values at any one of the two endpoints. Estimates are valid under the assumption that values are Missing at Random conditional on the baseline values and all outcome values included in the analysis. CIs will be estimated via a parametric bootstrap with 1000 bootstrap samples.

For all outcomes, we will report baseline and follow-up descriptive statistics. For the primary outcomes only, we will estimate the standardised effect sizes and therapist effects if feasible. Please see the further details in the Statistical Analysis Plan in online supplemental materials.

### Qualitative analysis

The qualitative interviews will be audio recorded, transcribed verbatim and analysed using Braun and Clarke’s thematic analysis.^57^ The aim is to understand participants’ experiences of receiving and providing the intervention, including its acceptability, safety and perceived usefulness. Analysis will be conducted on NVivo software. A critical realist perspective will be adopted, researcher reflexivity promoted and validity checks conducted. Service user interviews will be analysed first to give a primary voice to the experts by experience accounts.^58^ We will conduct credibility checks with participants. The theme structure will also be discussed with the NETp co-production group and research team. Please see further details in online supplemental materials.

### Economic analysis

For the early-stage economic analysis, the impact of the NET intervention on cost will be assessed compared with TAU. Health costs collected using the CSRI and QALYs (collected using the EQ-5D-5L) questionnaires will be compared at the baseline, 4-month and 8-month follow-up points and presented as mean values by study arm with SD. Unit costs from (available from the Personal Social Services Research Unit) and NHS Reference Costs will be used to generate NHS service costs. Lost work and informal care will be valued using average wage rates from the Office for National Statistics (ONS). Incremental QALYs and costs will be compared between each level of NET and routine care. In the case of one option having higher costs and producing more QALYs than another, we will present the incremental cost-effectiveness ratios to show the extra cost incurred to produce one more QALY. Uncertainty around the estimates will be explored using cost-effectiveness planes and acceptability curves.

### Patient and public involvement

Lived experience has been a core aspect of the project from the outset. We secured Public Involvement Fund (Ref: 5726) from the RDS East of England National Institute for Health and Care Research (NIHR) Research Design Service (RDS) to cover PPI costs during the application for NIHR funding. Two of the grant co-applicants are people with lived experience, including receipt of NET for PTSD while under the care of EIP. The Lived Experience NETp Co-Production Group, led by the trial PPI lead, includes service users under the care of EIP and has experienced multiple trauma and psychosis experiences and carers, with representation from minoritised backgrounds, a range of genders and ages. PPI has and will continue to shape all aspects of the study, from developing the trial and therapy protocols, selection of measures and procedures, shaping content of interview guides, conducting peer interviews, interpretation of findings and dissemination.

### Ethics and dissemination

This study was submitted to London - City & East Research Ethics Committee (REC) and has received REC/HRA ethical approval (25/LO/0350). Written informed consent will be gained from each participant before any study procedures are initiated. If amendments to the protocol are required, the same ethics committee will review them. UCL is the trial sponsor. (Email: [contact]). There are no trial criteria for discontinuing allocated interventions at the participant level, but participants will be made aware that if they find aspects of the research or therapy distressing and no longer want to continue, they will be able to withdraw without having to give a reason of this impacting on their routine clinical care.

The results of the study will be reported and disseminated at international conferences and in open-access peer-reviewed scientific journals. The results will also be available to participants and clinical teams in an accessible format and will be presented in a dissemination event. The study has a Trial Management Group overseeing the study, a Lived Experience NETp Co-Production Group as well as an independent Trial Steering Committee also supporting it.

